**II. FUNDING**

This study is supported with a grant from Patient Centered Outcome Research Institute under the category of Assessment of Prevention Diagnosis and Treatment Options.

**III. BACKGROUND AND SIGNIFICANCE**

Anxiety disorders (generalized anxiety disorder, social anxiety disorder, panic disorder, and agoraphobia) are associated with significant distress and impairment in social and occupational functioning [1] and increased risk for suicide [2]. While pharmacotherapy and psychotherapy are first-line treatment strategies for anxiety disorders, many patients are reluctant to take psychiatric medication, and many prefer to avoid psychiatric care due to stigma or distrust of traditional medical care [3-6]. Pharmacotherapy approaches including selective serotonin reuptake inhibitors (SSRIs) have shown efficacy in treating anxiety disorders, however, side effects and stigma associated with psychotropic medications limit their adoption. Although Cognitive-Behavioral Therapy also has recognized efficacy, it is typically provided in a psychiatric clinic (which is associated with stigma) and is limited by availability of trained psychotherapists [7, 8]. Thus, it is increasingly important to compare the effectiveness of standard treatments to alternatives which are offered outside of a mental health context and may have better patient acceptability.

Mindfulness meditation training has seen an exponential growth in popularity in the general public, as illustrated by results from the NIH National Health Interview Survey finding that 18 million adults in the US have now tried meditation [9]. Patients with anxiety disorders are interested in mindfulness [8, 10]. However, although mindfulness meditation is commonly used to target anxiety [11], there is no information about how it compares to SSRI medication which is currently the most widely used treatment for anxiety disorders [12].

Individuals with anxiety disorders who are considering trying mindfulness do not currently have any evidence-based information to help them make decisions about how this new strategy compares to standard treatments. This proposal aims to fill that gap. Other stakeholders, such as those from healthcare systems and payers need this information to help guide decisions about integrating mindfulness interventions into existing treatment options. If mindfulness meditation was just as effective as SSRI medication, which is considered first-line treatment in the field, this would support insurance reimbursement and wider implementation of mindfulness meditation treatments across healthcare domains.

Mindfulness practice involves focusing on current thoughts, feelings, and physiological sensations, and thus, mindfulness practice trains a person to act consciously rather than react unconsciously to external or internal stimuli [13]. By continually practicing being “mindful,” an individual learns to stay focused on present thoughts and emotions during stress, rather than getting distracted by anxiety-related sensations and worries, which can lead to better coping and more successful problem-solving behaviors [14]. Systematic mindfulness meditation training has been manualized in a group format called Mindfulness-Based Stress Reduction (MBSR). Several studies have already demonstrated positive findings for mindfulness meditation interventions in patients with anxiety [15-17]. In addition, our tightly-controlled, randomized trial of MBSR vs. an attention control in individuals with generalized anxiety disorder (35% with co-morbid anxiety disorders) yielded greater drops in several anxiety symptom scales assessed by blinded clinical raters (see *Preliminary Data* section below). Unfortunately, the critical lack of information about how mindfulness meditation training compares with existing treatments including SSRI medications, in terms of effectiveness and acceptability, prevents patients from being able to make informed decisions when choosing a treatment approach.

#### **IV. SPECIFIC AIMS (Research Objectives)**

We will assess the comparative effectiveness of Mindfulness-Based Stress Reduction (MBSR) compared to escitalopram (ESC) for patients with anxiety disorders (generalized anxiety disorder, panic disorder, agoraphobia, and social anxiety disorder), by randomizing patients to eight weeks of (1) MBSR or (2), flexible-dose escitalopram. This two-arm, three-site, randomized, controlled study will use a standard non-inferiority study design which incorporates previous data demonstrating that escitalopram is an effective treatment for anxiety and has been proven against pill placebo. Based on non-inferiority driven power calculations (see Analysis plan), we plan to randomize 368 patients to either MBSR or medication. We expect that 276 will complete the protocol after 25% dropout; however treatment satisfaction including dropout and intent-to-treatment outcomes will also be important assessments to guide conclusions about patient preferences and treatment responses. This non-inferiority randomized design with standardized blinded assessments provides the most rigorous comparison data regarding comparison of the novel treatment of MBSR to a gold standard treatment, escitalopram. This study will provide crucial information to patients about effective and acceptable treatment strategies for anxiety.

We will examine several secondary outcome measures and exploratory outcomes. Overall Anxiety Severity and Impairment Scale (OASIS) is the secondary measure of anxiety symptoms. To assess satisfaction/acceptability of treatment, we will use the Client Satisfaction Questionnaire (CSQ) and the Reactions to Treatment Questionnaire (RTQ). To assess sleep outcomes, we will use the Pittsburgh Sleep Quality Index (PSQI), The Beck Anxiety Inventory (BAI) is a 21-item self-report inventory designed to measure severity of anxiety symptoms in

psychiatric populations. The PROMIS - Emotional Distress scales (ED) will be used to assess emotional distress in the past 7 days, including depressive symptoms, anxiety symptoms, and anger. Other patient-reported measures include the Penn State Worry Questionnaire (PSWQ), and the Health Performance Questionnaire (HPQ). We will also use the Quick Inventory of Depressive Symptomatology, Self-Report, or QIDS-SR to measure depression severity including suicidality. Other clinician-reported outcomes include the Liebowitz Social Anxiety Scale (LSAS), the Panic Disorder Severity Scale (PDSS), the Structured Interview Guide for the Hamilton Anxiety Scale (SIGH-A), the Clinician Global Impression-Severity and Improvement Scales (CGI-S and CGI-I), and the Frequency, Intensity, and Burden of Side Effects Ratings (FIBSER).

## **V. SUBJECT SELECTION**

We aim to enroll 620 participants total across the three study sites (GUMC, NYU, and MGH Boston). With a projected dropout rate of 25%, we expect 465 completers. Subjects must be between 18-75 years of age, have an anxiety disorder, and agree to participate in this randomized controlled study in which they will be randomized to either an MBSR class or medication.

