Therefore, the null hypothesis for the non-inferiority test will be that the drug group's mean CGI-S score reduction at endpoint is greater than that of the MBSR group by at least 0.495 points (for this scale, higher scores indicate higher severity and greater reduction indicated greater improvement). In other words, if the MBSR group's post-intervention mean CGI-S score change is less than that of the drug group by not more than 0.495 points we will consider MBSR to be non-inferior to the standard pharmacotherapy escitalopram. Based on these parameters, the required analysis sample size with equal allocation to achieve an 80% power at significance level of 0.05 will thus be N=276 study completers.

To conservatively address attrition, we estimate our projected dropout rate to be 25% and therefore plan to randomize 368 participants with a 1:1 ratio to each group, yielding 276 completers after drop-out. Of note, many published non-inferiority trials have relied on intent-to-treat analyses that are more liberal than our proposed completer analysis. We also propose to conduct sensitivity analyses with the intent-to-treat sample as a follow-up to our primary completer analysis.

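### The protocol gives two incompatible sample sizes at the same 25% dropout, 620 enrolled with 465 completers and 368 randomised with 276 completers; only the second follows from its power calculation

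*Protocol*

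**What the plan says.** Section V (Subject Selection) of the protocol sets the total: "We aim to enroll 620 participants total across the three study sites". The next sentence derives the completers: "With a projected dropout rate of 25%, we expect 465 completers". The same paragraph requires that these subjects "agree to participate in this randomized controlled study in which they will be randomized to either an MBSR class or medication".

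Section IV (Specific Aims) has a different total: "we plan to randomize 368 patients to either MBSR or medication", followed by "We expect that 276 will complete the protocol after 25% dropout".

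Section VIII (Biostatistical Analysis, Outcome Assessment) agrees with Section IV and supplies the derivation. The sample size needed "to achieve an 80% power at significance level of 0.05 will thus be N=276 study completers". After an allowance of 25% for dropout, the investigators "plan to randomize 368 participants with a 1:1 ratio to each group, yielding 276 completers after drop-out".

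No section links the two pairs. There is no screen-failure allowance, no second cohort and no sample size re-estimation.

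**The concern.** A confirmatory non-inferiority trial needs one randomised number. A site or ethics board working from Section V would plan for 620; a statistician working from Section VIII would plan for 368. The two pairs share the same three sites, the same two arms and the same dropout rate, so neither a different dropout assumption nor a slip in one digit explains the difference.

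At stake is whether up to 252 further people are randomised without a stated reason or, if 620 is the intended target, whether recruitment ends 252 short of it.

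**Working it through.** **Inputs.** From Section V: 620 enrolled, 465 completers, 25% dropout. From Sections IV and VIII: 368 randomised, 276 completers, 25% dropout, 1:1 allocation, 80% power, significance level 0.05 with sidedness not stated. From Section VIII, Outcome Assessment: SD 1.1 for CGI change, margin 0.33 for the sample size calculation, margin 0.495 for declaring non-inferiority. I assume a true difference of zero.

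**Step 1: each pair on its own.** 368 × 0.75 = 276 and 620 × 0.75 = 465. Both multiplications are right, so the fault is an inconsistency between sections and not a calculation error within one.

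**Step 2: the pairs against each other.** 620 − 368 = 252 participants and 465 − 276 = 189 completers. The ratio is 1.685 in both cases, or 68% more. Since 465 is larger than 368, Section V expects more completers than Sections IV and VIII would randomise.

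**Step 3: reproduce the plan's figure.** The number per arm is 2 × (z for alpha + z for power)² × (SD / margin)². With one-sided 0.05 and 80% power this is 2 × (1.645 + 0.842)² × (1.1 / 0.33)² ≈ 137.4, rounded up to 138. The total is 276 completers, and 276 / 0.75 = 368 randomised. The plan's figures reproduce exactly.

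**Step 4: look for a source of 465 and 620.** The same formula at other settings, with 25% dropout:

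| Margin | One-sided alpha | Power | Completers | Randomised |
|---|---|---|---|---|
| 0.33 | 0.05 | 80% | 276 | 368 |
| 0.33 | 0.05 | 90% | 382 | 510 |
| 0.33 | 0.025 | 80% | 350 | 467 |
| 0.33 | 0.025 | 90% | 468 | 624 |
| 0.495 | 0.05 | 80% | 124 | 166 |
| 0.495 | 0.025 | 90% | 208 | 278 |

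The inputs that the protocol states do not give 465 and 620. The nearest row, 468 and 624, needs 90% power and one-sided 0.025, and the protocol states neither.

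**Step 5: what the choice does to power.** Power = Φ(margin / (SD × √(4 / N)) − z for alpha), with N the total number of completers.

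| Margin | One-sided alpha | N = 276 | N = 465 |
|---|---|---|---|
| 0.33 (planning) | 0.05 | 80.2% | 94.4% |
| 0.33 (planning) | 0.025 | 70.3% | 89.9% |
| 0.495 (decision) | 0.05 | 98.2% | 99.9% |
| 0.495 (decision) | 0.025 | 96.2% | 99.8% |

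For example, at margin 0.33 and N = 276: 0.33 / (1.1 × √(4 / 276)) = 2.492, and Φ(2.492 − 1.645) ≈ 0.802.

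**The case against.** The strongest defence is that 620 counts people consented or screened and 368 counts those randomised. Section V speaks of enrolling and the other two sections of randomising, and consent comes before the eligibility work-up, so a larger number before randomisation is plausible. As Section V is written, however, this fails. It applies the 25% to 620; if 368 of 620 were randomised, completers would be 276 (44.5% of 620) and not 465. It describes its subjects as people who will be randomised. Section VI also treats signing the consent form and enrolling as separate events. What stands is that 620 may be a mislabelled ceiling to which the dropout rate was wrongly applied. In that case 465 is still wrong.

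It can also be said that a careful reader can tell which pair is the design: 368 and 276 appear in two sections and are the only figures tied to allocation and power. That is fair, and it makes the correction easier. It does not remove the conflicting target from the section that governs enrolment.

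A reader might infer three stronger points that the document does not support.

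- **That the inconsistency leaves the trial underpowered.** With 0.05 read as one-sided, both sizes meet the stated 80% at either margin. The 70.3% in the table comes from the unstated sidedness of the significance level, which is a separate matter.
- **That the contrast of 80.2% with 94.4% is the effect on the trial's conclusion.** It holds only at the planning margin. At the margin used to declare non-inferiority, the difference is about 2 to 4 percentage points.
- **That two targets let someone choose when to stop on the results.** The protocol describes no interim efficacy look, and its independent evaluators are blinded to allocation, so this is speculation.

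**Conclusion.** The contradiction is real and the text is wrong as written: Section V cannot hold together with Sections IV and VIII. The discrepancy is 252 participants and 189 completers. Its consequence is an undefined recruitment target and up to 252 participants with no stated justification.

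The internal evidence favours 368 and 276, because only that pair can be derived from the stated inputs. This rests on reading 0.05 as one-sided and on a true difference of zero. It does not prove which number the sponsor intends. A reader might conclude that 620 is simply the error, but the protocol does not establish that, and a deliberate increase that was never carried into the other sections is also possible. The closeness of 620 to 624 in Step 4 is no evidence for either view, since it depends on unstated inputs.

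**What to change.** State one randomised number and one completer number, identical in Sections IV, V and VIII.

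- **If the current power section stands:** these are 368 and 276. Correct Section V and delete its figure of 465 completers. If 620 is a ceiling on people consented or screened, label it so and say that 368 of them are to be randomised.
- **If 620 randomised is intended:** revise Sections IV and VIII instead, and state the power, significance level with sidedness, margin and SD that justify 620 and 465.

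The first route costs a one-paragraph correction and adds no participants to the 368. The second needs a restated sample size calculation and means 252 more randomised participants than Sections IV and VIII now plan. Neither requires new data.

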### **Inclusion Criteria:**

1. Men and women between age 18 and 75 years old.
2. Have a primary anxiety disorder, including: social anxiety disorder (SAD), generalized anxiety disorder (GAD), panic disorder, or agoraphobia
3. Must understand study procedure and willing to participate in all testing visits, and treatment as assigned.
4. Participants must be able to give informed consent to the study procedures.

### **Exclusion Criteria:**

1. Comorbid psychiatric disorder other than anxiety or depression, such as psychotic disorder, obsessive compulsive disorder, eating disorders (i.e., anorexia and bulimia), bipolar disorder; developmental or organic mental disorders; and current (past 6 months) substance use disorders and current post-traumatic stress disorder as assessed by clinician at screening visit
2. A serious medical condition that may result in surgery or hospitalization.
3. A history of head trauma causing prolonged loss of consciousness, or ongoing cognitive impairment
4. Inability to understand study procedures or informed consent process, or significant personality dysfunction likely to interfere with study participation (assessed during the clinical interview).
5. Subjects who will be non-compliant with the study procedures. This may include planned travel out of town.
6. Pregnancy as assessed by urine test at screen. Avoidance of pregnancy is also necessary for inclusion in this study.
7. Subjects taking barbiturates, SSRIs, anti-depressants, or antipsychotics. Sleep medications (other than anti-depressants) and benzodiazepines will be allowed, if has been taken at stable dose 4 weeks prior to baseline and the patient plans to continue at the same dose through the trial. Trazadone (for sleep) above 100mg will be disallowed.

8. Concurrent psychotherapy initiated within 1 month of screen interview, or ongoing psychotherapy of any duration directed specifically toward the treatment of anxiety (such as Cognitive Behavioral Therapy).
9. Individuals who have completed a course of MBSR or an equivalent meditation training in the last year, or have an ongoing daily meditation practice.
10. Individuals reporting significant active suicidal ideation or suicidal behaviors within the past year.
11. Individuals with a medical condition (i.e., epilepsy) that may be exacerbated by study treatment, as determined by a study physician or nurse practitioner based on history, physical, and/or labs.

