## **VII. STUDY PROCEDURES**

Patients with anxiety disorders from nearby communities and in the surrounding metropolitan areas will be invited to participate through study recruitment materials. Participants may be engaged using IRB-approved print and radio advertisements and clinic referral at GUMC, NYU, and MGH. Participants may also be solicited through IRB-approved media, flyers, postings and other primary care and psychiatric clinic facilities and programs. Referrals may be made by medical and mental health practitioners in the area as well as self-referrals by affected individuals.

Individuals who contact the study coordinators at each site will be phone screened for general medical and diagnostic treatment eligibility and interest in research participation. If they are eligible and interested, they will then have a meeting with a study clinician to evaluate their psychiatric diagnosis and eligibility. This first visit (Screening Visit) includes a psychiatric (using the MINI interview) and medical assessment and brief physical exam, to determine eligibility. The study clinician will inquire whether the participant has a primary care clinician or psychiatrist who already did a medical work up to rule out medical causes of anxiety symptoms. If they have, staff will ask the participant to sign a release form in order to give permission to speak with the participant's doctor or to provide the study team with a copy of past blood tests or ECG

or if neither a confirmation from records or the outside provider is not possible, study staff will perform an ECG and blood test.

For all participants, urine testing for pregnancy and drugs of abuse will be completed to help determine whether exclusion criteria are met (pregnancy, substance abuse) by the research coordinator. The Screening Visit will take about 3 hours. The study will be open to adults 18 – 75 years old who have an anxiety disorder; all races, and ethnicities and genders are invited. We will repeat the Screening Visit if extenuating circumstances lead to an abnormally long waiting time between the Screening Visit and Baseline Visit, in order to obtain the most accurate and up-to-date information.

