The second study visit in the Baseline Assessment visit, which takes place within the 6-week period before the start of treatment. If unusual circumstances prevent the participant from beginning treatment within the 6-week window following the Baseline Assessment, the visit will be repeated to obtain the most accurate and up-to-date information. Patients will be assessed by the “Independent Evaluator” who will remain blind to treatment allocation, and who will complete the clinician-rated instruments (please see Table of Assessments). Assessments will be made by trained, independent evaluators (IE's) either in person, by videoconferencing, or by phone. If assessments are completed by videoconferencing or phone due to concerns of coronavirus, we will omit collecting vital signs and weight at that visit. All IEs for this multicenter trial will be undergoing shared training and supervision across sites. If necessary, IE's can assess patients at any of the study sites. Patients will be asked to complete a series of patient-reported questionnaires (please see table that consist of questions about the participants' thoughts, feelings, anxiety symptoms, depression symptoms, adverse and traumatic experiences in the past, sleep, and other topics; these will be repeated in subsequent study visits (see Table of Assessments).

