| Sleep ( PSQI, PROMIS-sleep anxiety measure )                    |        | ✖                         |        |        | ✖      |        | ✖                      |                    | ✖                  |
| Quality of Life/Functioning                                     |        | ✖                         |        |        | ✖      |        | ✖                      | ✖                  | ✖                  |

|                                                          |   |    |   |   |   |   |   |   |   |
|----------------------------------------------------------|---|----|---|---|---|---|---|---|---|
| (PROMIS- SPSR and PROMIS- APSRA-8)                       |   |    |   |   |   |   |   |   |   |
| Adverse Experiences (CTQ and LEC)                        | ✖ |    |   |   |   |   |   |   |   |
| Work performance (HPQ)                                   |   | ✖  |   |   |   |   |   |   | ✖ |
| Clinician-rated assessments of outcome                   |   |    |   |   |   |   |   |   |   |
| Psychiatric Diagnoses (MINI)                             | ✖ |    |   |   |   |   |   |   |   |
| Anxiety symptom severity (CGI-S /CGI-I)                  |   | ✖  |   |   | ✖ |   | ✖ | ✖ | ✖ |
| Disorder-specific scales (PDSS, SIGH-A, LSAS)            |   | ✖  |   |   | ✖ |   | ✖ | ✖ | ✖ |
| Measures of Safety and Study Integrity                   |   |    |   |   |   |   |   |   |   |
| Side Effects (FIBSER & Adverse Events)                   |   |    | ✖ | ✖ | ✖ | ✖ | ✖ | ✖ | ✖ |
| Adherence/ Homework                                      |   |    | ✖ | ✖ | ✖ | ✖ | ✖ | ✖ | ✖ |
| Depressive symptoms (QIDS-SR including suicidality item) |   | ✖  |   |   | ✖ |   | ✖ | ✖ |   |
| Vital Signs                                              | ✖ |    |   |   | ✖ |   | ✖ |   |   |
| Clinician Suicide Assessment                             | ✖ | ✖* | ✖ | ✖ | ✖ | ✖ | ✖ | ✖ | ✖ |
| Concomitant Treatment                                    | ✖ | ✖* | ✖ | ✖ | ✖ | ✖ | ✖ | ✖ | ✖ |
| Weight                                                   | ✖ |    |   |   | ✖ |   | ✖ |   |   |
| Blood draw, ECG, Urine pregnancy/drug test**             | ✖ |    |   |   |   |   |   |   |   |

\*these measures will be repeated with MD/NP during first week of treatment (referred to as “week 0”) unless the participant has been randomized to MBSR *and* less than two weeks elapse between that participant’s baseline visit and the start of their treatment)

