#### Escitalopram (ESC)

During the 8 weeks of randomized treatment with ESC, subjects will be seen at baseline, post-baseline medication pick-up visit, weeks 1, 2, 4, 6, and 8 week endpoint, and at 12 week follow-up, (9 visits total) by a study physician/nurse practitioner. Georgetown University Medical Center's research pharmacy will be responsible for preparing the medication, which will be given to the participants by a study M.D. from baseline to week 12. Patients will take the pills each day at home. ESC will be initiated at 10 mg/day; which will be continued to week 2, when it will be increased to 20mg/day if well tolerated (or delayed if not). Medication adherence will be assessed by pill count and a standardized adherence measurement [68]. Side effects will be assessed at each visit and recorded. Participants will also be instructed to contact study staff immediately if any significant side effects, symptomatic worsening, or suicidal ideation develops in between visits. After week 12, if the patient desires to stay on the medication, s/he will be given a prescription by the study MD/NP., who will also start the process of transition to outpatient care so that the patient can continue treatment after the end of the study, if desired.

If in-person visits are not possible for any reason (e.g., coronavirus), the study medication will be shipped directly to the patient from the research pharmacy following the pharmacy protocols and the study visits will be conducted using telehealth videoconferencing or telephone contact.

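### The protocol schedules a urine pregnancy test only at Screening, so escitalopram may be started on a negative result 42 days old or older, with no re-test scheduled before dispensing

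*Protocol*

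**What the plan says.** - **Eligibility.** Section V, Exclusion Criteria, item 6: "Pregnancy as assessed by urine test at screen. Avoidance of pregnancy is also necessary for inclusion in this study".
- **Screening Visit.** Section VII says that for every participant "urine testing for pregnancy and drugs of abuse will be completed to help determine whether exclusion criteria are met". The preceding paragraph allows outside records to stand in for the ECG and the blood test; it does not mention the urine test.
- **Table of Assessments.** The row "Blood draw, ECG, Urine pregnancy/drug test" has a single mark, under Screen. It carries the double-asterisk footnote, under which the row's procedures are done only when earlier records cannot be obtained.
- **Screening to Baseline.** "We will repeat the Screening Visit if extenuating circumstances lead to an abnormally long waiting time between the Screening Visit and Baseline Visit". No number of days is given.
- **Baseline to treatment.** The Baseline visit is one "which takes place within the 6-week period before the start of treatment", and this window is the same for both arms. For a start later than that, Section VII sets this rule: "If unusual circumstances prevent the participant from beginning treatment within the 6-week window following the Baseline Assessment, the visit will be repeated".
- **Week 0.** The single-asterisk footnote says "these measures will be repeated with MD/NP during first week of treatment". It is attached to the suicide assessment and concomitant treatment rows only.
- **Dispensing.** In the Escitalopram (ESC) section, "subjects will be seen at baseline, post-baseline medication pick-up visit, weeks 1, 2, 4, 6, and 8 week endpoint". The same section lets the pharmacy ship the drug when in-person visits are not possible.
- **Risk statement.** Section IX (v) says that information on escitalopram in pregnancy and breastfeeding is insufficient, that a woman who is already pregnant may not take part, and that a woman who becomes pregnant must tell the study at once.

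**The concern.** Pregnancy is an exclusion that can newly arise between the test and the first dose. The schedule fixes the test at the earliest visit and then allows a long wait, and nothing listed after Screening checks the criterion again. Followed as written, it permits dispensing to a woman who conceived after her screening test and does not yet know it. By the protocol's own rules she should not be in the trial.

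The duties to avoid and to report pregnancy do not reveal a pregnancy that the woman has not recognised. The records footnote adds a second weakness: on its literal wording, the one scheduled test might not be done at all if an older record is available. What is at stake is participant safety and the correct application of an eligibility criterion, not the estimand or the analysis.

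**Working it through.** The protocol states no figure for the age of the pregnancy test at first dose, so there is none to reproduce. The check adds intervals and compares passages.

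**1. Age of the result at first dose**

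Inputs: baseline-to-treatment interval of at most 6 weeks (Section VII, Baseline Assessment visit); screening-to-baseline gap g, not given.

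Age = g + (Baseline to first dose) ≤ g + 6 weeks, as long as treatment starts within the window.

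| Assumed g (not in the protocol) | Oldest result permitted within the window |
|---|---|
| 0 weeks | 6 weeks = 42 days |
| 2 weeks | 8 weeks = 56 days |
| 4 weeks | 10 weeks = 70 days |

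**2. Does any rule renew the test?**

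- *Repeat of Screening.* This would renew the test. It is triggered by an abnormally long wait between Screening and Baseline, with no threshold, so it sets no hard limit.
- *Repeat of Baseline after a missed window.* The Baseline column has no pregnancy test, so the repeat does not itself renew the result. It does lengthen the interval from Screening to the operative Baseline, so it might lead to a repeat of Screening. The text does not settle this.
- *Week-0 repeat.* It covers suicide assessment and concomitant treatment. Its only exemption is for MBSR participants who start less than two weeks after Baseline, so every escitalopram participant has these two items checked again. Pregnancy is not among them.
- *Medication pick-up visit.* No test is listed, but the visit has no column in the table and its content is not described.

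Pregnancy tests scheduled in this document between Screening and first dose, unless Screening is repeated: 0.

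**3. Do the passages on the screening test agree?**

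On timing they do: criterion 6, the Screening Visit text and the table all say Screening. On whether the test is always done they do not. The Screening Visit text tests everyone and limits the use of records to ECG and bloods. The double-asterisk footnote applies the records exception to the whole row, which includes the urine pregnancy test.

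**4. Ceiling on the number of added tests**

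With 1:1 allocation (Section VIII, Outcome Assessment): 368 / 2 = 184. If all 620 whom Section V aims to enrol were randomised: 620 / 2 = 310. Both count every escitalopram participant; men and women not of childbearing potential reduce them.

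**The case against.** **Silence about the pick-up visit.** A reader might infer that no woman is re-tested before receiving drug. The document does not support that. The pick-up visit has no table column, shipping follows pharmacy protocols that are not shown, and Section IX refers to risk-minimising procedures in a section 9.3 that is not in this text (cited there for suicidality). A test could be done under one of these. What stands is that none is scheduled in this document, and a safety check that eligibility depends on belongs in the visit schedule.

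**Delayed starts.** It is also tempting to say that a missed window leads only to a repeat of Baseline. That is too strong, because the rule for repeating Screening could then apply. Its undefined trigger still leaves the age of the test without a limit.

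**Existing safeguards.** Avoiding pregnancy is a condition of inclusion, notification is required, and escitalopram participants see a physician or nurse practitioner at pick-up, during treatment and at week 12. Participants are therefore not unmonitored. None of this detects an unrecognised pregnancy before the first dose.

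**Where the line is drawn.** Study drug is given through week 12, and this point asks for no on-treatment test, relying there on the same duties that it finds insufficient before the first dose. The difference is that current pregnancy is a stated exclusion, so the check should be recent when exposure begins. Whether to test during treatment is a separate judgement.

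**Weight.** Section IX describes a widely used, well-tolerated drug and speaks of insufficient information rather than known harm. That keeps this below a critical defect; it does not remove the case for an inexpensive check.

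**Conclusion.** The concern holds for what the document schedules. The pregnancy test is placed at Screening only, and a negative result may be 42 days old at the first escitalopram dose even if Screening and Baseline fall on the same day. It may be older by a screening-to-baseline gap that has no numeric cap. In addition, the records footnote conflicts with the statement that all participants are tested.

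The 42 days assumes that the full baseline-to-treatment window is used and that Screening is not repeated. A reader might infer that such delays are usual or that a certain number of pregnancies would be exposed. The document gives no distribution of start times, no share of women of childbearing potential and no conception rate, so no expected count can be claimed. This is an avoidable safety weakness that should be corrected; it has no effect on the trial's statistical conclusions.

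**What to change.** 1. Add a column or footnote to the Table of Assessments for the post-baseline medication pick-up visit. It should require a negative urine pregnancy test, for women of childbearing potential randomised to escitalopram, before drug is dispensed.
2. Where drug is shipped, send a home test and require the result to be reported before shipment.
3. Remove the urine pregnancy test from the double-asterisk records exception, so that the table agrees with the Screening Visit text.

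The result would then be as old as the interval from pick-up to first dose (0 days if both fall on the same day). For shipped drug, the interval runs from the home test and includes delivery time.

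**Cost.** One additional urine strip per eligible woman, with a ceiling of 184 on the 368 planned (310 if all 620 were randomised), at a visit that already takes place and with a test the trial already uses. Shipped drug may be delayed a little while the result is awaited. Very recent and later conceptions would still be missed, so the avoidance and notification duties must stay. Nothing in the analysis changes.
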